#### Safety

Since this study is observational, there are no direct risks associated with participation.

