## Materials and methods

### Study design

A pre-post study will be conducted prospectively among hemodialysis patients at the Hemodialysis Unit, Hospital Kuala Lumpur (HKL), and the Hemodialysis Affiliated Centers of the University Malaya Medical Centre (UMMC). The selected patients will be followed for a period of 12 months. The estimated sample size using a power of 0.95 and 95% confidence interval was 56 patients.

$$n>={\left\{\begin{array}{c} Z_{\alpha /2}+Z\beta \\ ES \end{array}\right\}}^{2}$$

n = sample size

Z = statistic for level of confidence, using a 95% confidence interval (so Z = 1.96)

α = 0.05

β = type 11 error

ES = Effect size, δ / σ

δ = A difference in population means

σ = Standard deviation of difference in the response of matched pairs

Therefore, by using value of δ = 0.9 and σ = 1.84 from similar previous study on chronic illness patient [21].

n = 56

Study of a continuous response variable from matched pairs of study subjects. Prior data indicate that the difference in the response of matched pairs is normally distributed with standard deviation 1.84. If the true difference in the mean response of matched pairs is 0.9, we will need to study 56 pairs of subjects to be able to reject the null hypothesis that this response difference is zero with probability (power) 0.95. The Type I error probability associated with this test of this null hypothesis is 0.05.

**≈** 56 ± 25% * (to compensate for drop off or incomplete data)

≈ 70 respondents

*considering dropout rate of 25%, 14 patients were added; therefore total will be 70 patients altogether.

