### Outcomes measured

#### Primary outcome

Measuring the number of medication-related problems. All medication-related problems will be classified using the Pharmaceutical Care Network Europe (PCNE) classification version 9.00, which was last updated in June 2019 [25]. This is an established system for medication-related problem classification. With it, medication-related problems are categorized into nine primary domains for DRP causes. This tool has been validated to measure medication related problems among chronically ill patients [26]. Medication discrepancies are categorized in Table 1. Identification of medication record discrepancies included in this study follows previous literature [27, 28].

**Table 1 pone.0263412.t001:** Medication record discrepancy.

Unintentional Discrepancy: medication change made either inadvertently or deliberately by the patient without the knowledge of the health care team. Undocumented Intentional Discrepancy: medication change made by another healthcare professional but not listed on the medication record. Subcategories include: ● omission (medications being taken by the patient but not listed in the medication record) ● commission (medications no longer being taken by the patient but still listed on the medication record) ● wrong drug ● wrong dose ● wrong frequency ● dose/schedule not listed

Source: Medication record discrepancy [22,23].

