### Interventions

Two interventions will be provided in this study: medication review and motivational interviewing.

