#### a) Medication review

MR is a well-structured method to optimize medication use and improve health outcomes among patients [31]. The researcher will examine patient medical records and interview patients to identify patient medication discrepancies and medication-related problems. Any medication issue related to a patient’s medicine-taking behavior and use of medicine in the context of their clinical condition will be recorded. The PCNE version 9 and kidney-related clinical practice guidelines will be used as guides. All the recorded medication problems will be discussed with relevant physician. The changes done by the physician will be notified to the researcher and can be tracked in the following follow up.

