### Study procedure and follow up

Once informed consent is obtained from the eligible patients at the first month’s visit, patients’ medication adherence, QOL and lab results—mainly the calcium, phosphate, hemoglobin, lipid profile, and glycosylated hemoglobin levels will be assessed. A medication review will also be performed. The updated list and observations/recommendations will be provided to the physician in charge. The medical records will be reviewed in the following six months to determine whether individual discrepancies have been corrected and whether MRP recommendations have been accepted by the prescriber. Motivational interviewing will be conducted in 3 sessions, in the 3^rd^, 6^th^ and 9^th^ months. Each session will last approximately 15 to 20 minutes for each patient. Only the first session will be done face to face (during the patient’s scheduled dialysis day) to build a good relationship with the patient, while the second and third sessions will be conducted over the phone to minimize close contact with the patients during the COVID-19 outbreak period. This method has proven its efficacy in previous research [37] and ensures safety for both patients and the researcher. The number of sessions to motivate and improve medication adherence has been set at three, as the optimal number is not known [38–40]. At the final visit (12 months), the medication review will be performed, medication adherence, QOL score and lab parameters will be assessed. The pre-post results will be checked for significance in improvement using the software package Statistical Package for Social Sciences (SPSS) Version 26.0. The results will be evaluated to check if there are any significant changes in the number of medication-related problems, adherence and QOL at the end of patient-centered pharmacist care. The summary of study procedure is shown in Fig 1.

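### The Safety section infers no direct risk from an observational label that the rest of the article contradicts: the study delivers two interventions that can prompt medication changes

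*Protocol article*

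**What the plan says.** The Safety section consists of one sentence: "Since this study is observational, there are no direct risks associated with participation". No other ground for the absence of risk is given.

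Elsewhere the article describes something different:

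- Study design: "A pre-post study will be conducted prospectively among hemodialysis patients", with 12 months of follow-up and 70 patients to be recruited.
- Interventions: "Two interventions will be provided in this study: medication review and motivational interviewing".
- Medication review: "All the recorded medication problems will be discussed with relevant physician", and then "The changes done by the physician will be notified to the researcher and can be tracked in the following follow up".
- Study procedure and follow up: "The updated list and observations/recommendations will be provided to the physician in charge". Motivational interviewing follows in months 3, 6 and 9, and the medication review is repeated at 12 months.

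The primary outcome is given as "Measuring the number of medication-related problems". The secondary outcomes are adherence, quality of life and laboratory values. The six-month record review is to establish "whether individual discrepancies have been corrected and whether MRP recommendations have been accepted by the prescriber".

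**The concern.** A study that only watches usual care can fairly say that taking part adds no direct risk. A study that reviews each patient's medicines, sends recommendations to the prescriber and works on the patient's medicine-taking cannot use that argument. Here the argument is the whole of the safety rationale.

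The Study strengths & limitations section itself describes dialysis patients as being at high risk, with high mortality and morbidity. If the safety position rests on a wrong study type, nothing in the article explains why harm following an accepted recommendation need not be looked for. Fewer medication-related problems or better adherence could then be reported as benefit with no planned display of hospital admissions or deaths beside them.

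**Working it through.** No figure in the plan bears on this point, so the check sets the sections side by side.

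**Step 1: is the study observational on any reading of the article?**

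| Section | What it describes | Consistent with observational? |
|---|---|---|
| Safety | Observational, hence no direct risk | (the statement under test) |
| Study design | Prospective pre-post study | Neutral: this names the comparison, not who assigns the care |
| Patient centered pharmacist care | The study implements two methods of pharmacist care | No |
| Interventions | Two interventions are provided by the study | No |
| Medication review | Problems are taken to the physician; resulting changes are reported back and tracked | No |
| Study procedure and follow up | Recommendations go to the physician in charge; three interviewing sessions | No |
| Discussion | The model goes beyond the current renal adherence clinic, which centres on education and counselling | No: this is not existing practice being observed |

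Every section that describes what is done to participants describes an intervention. The Safety section stands alone.

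**Step 2: does the no-risk conclusion survive without the label?** The sentence derives the absence of direct risk from the study being observational and offers nothing else. Once the label goes, the conclusion has no stated support. That does not show the interventions to be harmful; it shows that the article gives no valid reason for ruling harm out.

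**Step 3: would the data named in the article show harm anyway?**

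- *Primary outcome:* the number of medication-related problems. Some drug-related harm could appear among these, since the review takes in any issue with the use of medicines and is repeated at 12 months. It reaches only patients who are still followed at that time.
- *Secondary outcomes:* adherence, quality of life, and glucose, calcium, phosphate, hemoglobin and LDL at baseline, month 6 and the end. Some harm could move these values, but none is tied to a medication change.
- *Six-month record review:* correction of discrepancies and acceptance of recommendations. These are process measures and say nothing about what happened to the patient afterwards.
- *Hospitalisation:* in the methods it occurs only in the text following Fig 1, as a reason for more than three missed appointments, after which exclusion of the patient may be decided.
- *Death:* not named as something to record.

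Drug-related problems and laboratory shifts thus have an indirect route into the data. Hospitalisation and death have none in the text shown, and a patient who deteriorates may leave the analysed group.

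**The case against.** Four points can be made for the plan.

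1. *The physician decides on every change.* True. The study prompts changes and does not make them, and only patients whose physician accepts a recommendation are exposed to one. But prompting changes and tracking their uptake is still intervention, so the label remains wrong.
2. *This is a condensed article.* A reader might infer that harms are not captured at all. The article does not support that: the full protocol is not shown and may contain adverse-event procedures. What stands is narrower. The article states a wrong study type and draws a safety conclusion from it, which is an error in what is written and not an omission.
3. *The repeat review, the laboratory values and routine three-monthly bloods with nephrologist review would reveal harm.* In part they would, so it would be too strong to say that there is no way to see adverse drug effects. None of them is set up as safety recording or linked to accepted recommendations.
4. *Ethical approval was obtained.* A reader might infer that the ethics committees were told the study was observational and must now be told of a reclassification. The article reports the approvals but not how the committees classified the study, and it speaks of interventions throughout. That inference has no support.

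**Conclusion.** The point holds as an internal contradiction with a practical consequence. The Safety section must be reconciled with the sections on patient-centred care, interventions and study procedure, and the no-risk conclusion cannot rest on the word *observational*.

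It has no numerical size. All 70 planned participants are to receive both interventions, but the number who will have a medicine changed is not given, and no event rate is stated from which a risk could be calculated. A bound computed from an assumed count of zero events would not measure this defect, and zero hospitalisations and deaths over 12 months is not a realistic scenario in a group the article calls high risk.

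The contradiction rests on the article's wording alone. The remark on event recording is limited to the text shown and assumes nothing about the full protocol. The primary analysis and the sample size are unaffected.

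**What to change.** 1. Rewrite the Safety section to say that this is a single-arm interventional pre-post study in which medication review may lead to changes made by the physician, and delete the inference from *observational* to no direct risks.
2. From the medical records already being reviewed, extract hospitalisations, deaths and suspected adverse drug events, each with its date relative to any accepted recommendation.
3. Report these descriptively for all enrolled patients, including any later excluded after missed appointments. If the full protocol already provides for this, a sentence pointing to it is enough.

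A before-and-after comparison with the year preceding consent should not be added. Nobody who consents can have died beforehand, so the death count before consent is zero by construction. Patients are also eligible after only 3 months of hemodialysis, so for some most of that year would precede dialysis.

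The cost is one corrected paragraph and a few extra data fields; no outcome, sample size or test changes. The limit is that, without a control group, the events describe what happened and cannot be attributed to the intervention.

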#### Statistical analysis

Continuous variables will be expressed as mean ± standard deviation or median and interquartile range. Categorical variables will be expressed as a percentage. Adherence and QOL patterns before and after intervention will be assessed using paired sample t-tests or Wilcoxon signed-rank tests, depending on the sample distribution. Pearson correlation coefficient or Spearman rank correlation coefficient tests will be used to evaluate the associations between adherence and QOL. A general linear model will be applied to find the factors associated with MRPs, adherence and QOL. Data will be analyzed using SPSS Version 26.0. The significant level will be set at p < 0.05.

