## Abstract

**Background:**

Patients requiring hemodialysis (HD) often have several chronic comorbidities, which necessitate the use of several medications and hence put them at high risk of polypharmacy. Medication-related problems (MRPs) among HD patients are a serious issue as they can increase morbidity and nonadherence with medications. To overcome this issue, a unique pharmacy practice model including medication review (MR) and motivational interviewing (MI) is needed to improve medication adherence, by reducing MRPs and optimizing therapeutic outcomes. The present study aims to assess the effectiveness of MR and MI in improving medication adherence, quality of life (QOL) and clinical outcomes among end-stage renal disease (ESRD) patients who are on dialysis.

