**Discussion:**

We hypothesize that the implementation of pharmacy-based MR and MI may expect an increase in medication adherence scores and increase in HRQOL scores from baseline as well as achieving the clinical lab parameters within the desired range. This would indicate a need for a pharmacist to be involved in the multidisciplinary team to achieve a positive impact on medication adherence among hemodialysis patients.

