Information about the quality of life and adherence among hemodialysis patients in Malaysia is limited to reporting the incidence rate. To date, there is a paucity of information regarding the effectiveness of reducing MRPs and improving adherence using MI techniques among ESRD patients who are on dialysis [20]. In addition, there is no MI component in the renal medication therapy adherence clinic practice. The relationship between MRPs and QOL among HD patients has rarely been studied in Malaysia. Moreover, a previous study on improving adherence among HD patients uses only one component, either MR or MI, to show effectiveness. To date, no study has used a combination of these two interventions to create sustainable behavioral change for adherence to medication. **Hence, this study will evaluate the effectiveness of MR and MI in improving dialysis patients’ adherence, QOL and clinical outcomes.**

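### The number of medication-related problems is named primary, but the aim, the hypothesis and the paired-test sentence cover only secondary outcomes

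*Protocol article*

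**What the plan says.** Under Outcomes measured, the Primary outcome section opens with "Measuring the number of medication-related problems". Adherence (GMAS), quality of life (KDQOL-36) and laboratory values come under Secondary outcomes.

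The aim does not follow that order. The abstract's Background says "The present study aims to assess the effectiveness of MR and MI in improving medication adherence, quality of life (QOL) and clinical outcomes", and the Introduction closes in the same terms: "this study will evaluate the effectiveness of MR and MI in improving dialysis patients’ adherence, QOL and clinical outcomes". The hypothesis, in the abstract's Discussion, is that the intervention "may expect an increase in medication adherence scores and increase in HRQOL scores from baseline as well as achieving the clinical lab parameters" in the desired range. The next sentence there infers from this that a pharmacist belongs in the team.

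The Statistical analysis section assigns before-after tests as follows: "Adherence and QOL patterns before and after intervention will be assessed using paired sample t-tests or Wilcoxon signed-rank tests, depending on the sample distribution". MRPs enter that section only as one of three responses in a general linear model that looks for associated factors. The significance level is 0.05, with no order among outcomes.

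Two places do bring MRPs in. Study procedure and follow up says the results will be examined for "any significant changes in the number of medication-related problems, adherence and QOL". The main Discussion puts a lower rate of medication problems first among four expected results.

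**The concern.** A primary outcome has to be the one the aim asks about, the hypothesis predicts and a stated test decides. Here the label sits on one outcome, while the aim, the hypothesis and the named paired tests sit on others. A factors model does not fill the gap: it asks which characteristics go with MRPs, not whether their number changed.

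At stake is what the trial can conclude. Suppose the MRP count does not change and one quality-of-life scale reaches p < 0.05. By the outcome labels, the primary result is null. By the abstract's hypothesis, part of the prediction has come true. The article does not say which reading governs, and the choice should not be left until the 12-month results are known.

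**Working it through.** **1. The passages side by side**

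| Place in the article | MRPs | Adherence | QOL | Labs |
|---|---|---|---|---|
| Primary outcome | yes | – | – | – |
| Secondary outcomes | – | yes | yes | yes |
| Aim (abstract Background; Introduction) | no | yes | yes | yes |
| Hypothesis and inference (abstract Discussion) | no | yes | yes | yes |
| Study procedure and follow up, significance check | yes, test not named | yes | yes | not in that sentence |
| Statistical analysis, paired tests | no | yes | yes | no |
| Statistical analysis, factors model | yes | yes | yes | no |
| Main Discussion, expected results | yes, listed first | yes | yes | yes |

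The intention to test laboratory changes comes from the Secondary outcomes section, again without a named test.

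**2. Does the sample size settle which outcome leads?** The Study design section gives δ = 0.9, σ = 1.84, two-sided α = 0.05 and power 0.95, and states 56 pairs.

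n = [(1.960 + 1.645) × 1.84 / 0.9]² = 54.3, so 55. The exact paired t calculation at n = 56 gives power 0.949.

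The stated 56 therefore reproduces to within one patient. But the response is described only as a continuous variable from a study in chronic illness. The calculation does not say whether the 0.9 refers to MRPs, GMAS or something else, so it cannot resolve the mismatch.

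**3. Number of secondary tests**

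- GMAS total: 1
- KDQOL-36: burden, effects, symptoms, PCS and MCS = 5, or 6 with the optional kidney component summary
- Laboratory: glucose, calcium, phosphate, hemoglobin and LDL = 5

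Total: 1 + 5 + 5 = 11, or 1 + 6 + 5 = 12. The paired-test sentence alone covers 1 + 5 = 6 or 1 + 6 = 7.

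**4. Chance of at least one p < 0.05 if nothing changes.** Under independence this is 1 − 0.95^k. For correlated outcomes it was simulated (400,000 draws, equal correlation ρ). The values of ρ are assumptions; the article gives none.

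| k | Independent | ρ = 0.3 | ρ = 0.5 |
|---|---|---|---|
| 6 | 0.265 | not run | not run |
| 7 | 0.302 | 0.271 | 0.229 |
| 11 | 0.431 | 0.373 | 0.303 |
| 12 | 0.460 | 0.397 | 0.319 |

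Counting only false results in the favourable direction, under independence: 1 − 0.975^11 = 0.243 and 1 − 0.975^12 = 0.262.

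**5. The opposite decision rule.** If every outcome had to be significant, the chance of a false overall claim could not exceed that of any one test, so it would be at most 0.05. The error rate thus depends on a decision rule that the article does not state.

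**The case against.** The strongest reply is that a test of MRPs is planned. Study procedure and follow up lists MRPs first among the outcomes to be checked for significant change, the design is paired, and the level is 0.05. The main Discussion puts fewer medication problems first and draws its conclusion about pharmacists from the whole set. The abstract also presents reducing MRPs as the route to better adherence. Exactly one outcome is labelled primary, and a condensed article may leave the exact test and any hierarchy to a fuller plan. The paired-test sentence omits the laboratory values too, so it may not be a complete list.

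Much of this stands. A reader might infer that the primary outcome will not be tested at all, or that the conclusion will rest on secondary outcomes alone. The article does not support either reading, because of the two places just cited. Nor is a missing test name, taken alone, a fault in an article.

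A reader might also take 43-46% as the trial's false-positive rate. That is not supported either. No section says one positive result is enough, and both the abstract's hypothesis and the main Discussion join the outcomes with words meaning and.

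The conflict itself remains. The follow-up section gives MRPs no precedence over adherence and QOL, and the main Discussion does not say which of its four results decides. An unseen analysis plan could add a test, but it would not change an aim and a hypothesis that omit the primary outcome. The article is not silent on tests: it assigns paired tests to two secondary outcomes and gives the primary only a different kind of analysis.

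**Conclusion.** The concern holds as an internal inconsistency. The outcome labelled primary is absent from both statements of the aim, from the hypothesis and the inference attached to it, and from the sentence that assigns paired tests. Elsewhere it is to be checked for change, but without a named test or any statement that it decides. The article therefore offers differing criteria for success.

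The size depends on the decision rule. If any one of the 11 to 12 secondary tests could carry the claim, the chance of at least one false positive would be 43-46% under independence and about 30-40% at assumed common correlations of 0.3 to 0.5. For the 6 to 7 scores with named tests, it would be 26-30% under independence. If all outcomes had to improve, it would be at most 5%. These figures show what an unstated rule leaves open; they are not an estimate of the trial's actual error rate. The inconsistency does not depend on them.

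**What to change.** Reconcile the abstract (Background and Discussion), the end of the Introduction, the Primary outcome section, Study procedure and follow up, and Statistical analysis:

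- State that the change in the number of MRPs per patient, from the baseline review to the 12-month review, is the single outcome that decides the conclusion. Add it to the aim and the hypothesis.
- Extend the paired-test sentence to MRPs, using the Wilcoxon signed-rank or paired t-test already in the plan. A paired count model would also be acceptable but is not needed to close the gap.
- Label adherence, QOL and laboratory results as supportive.
- If the sponsor intends adherence to lead, relabel the GMAS total as primary and MRPs as secondary, before 12-month data are seen.

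The cost is wording only; no visit or measurement changes. The downside is that an isolated significant secondary result can no longer carry the headline conclusion.
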